**Methods:**

Randomized Controlled trial in parallel in healthy sedentary pregnant women (*n* = 265), Walking_Preg Project (WPP), from university hospital in Granada, Spain. At 12th gestational week (GW), they will be invited to participate and randomly assigned to one of the three arms of study: the intervention group I1 (pedometer, goal of 11,000 steps/day), intervention group I2 (pedometer, no goal) and control (no pedometer). Duration of intervention: 13–32 GW. At 12th, 19th and 31st GW the average steps/day will be measured in groups I1 and I2. At 13th, 20th and 32nd GW, Athens Insomnia Scale (AIS), Pittsburgh Sleep Quality Index (PSQI), Adherence to Mediterranean Diet (AMD), physical activity (short IPAQ), quality of life (PSI), and consumption of toxic substances (caffeine, illegal drugs, alcohol and tobacco) will be collected. Student t test or Mann-Whitney U will be used to compare 19th and 31st GW mean of daily steps between I1 and I2 groups. To compare differences between groups in terms of frequency of insomnia/quality of life for each trimester of pregnancy, Pearson’s Chi-square test or Fisher’s exact test will be used. To determine differences in hours of sleep and quality of sleep throughout each trimester of pregnancy, analysis of variance or Friedman test will be used. McNemar-Bowker test will be used to assess differences in life quality in pre-post analyses in the 3 arms. We will use Stata 15 statistical software.

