### Arms and interventions

The three groups will receive information about the recommendation of physical activity during pregnancy, according to ACOG guidelines [19].

#### Arm 1

Intervention 1 (I1), maximum intervention: pedometer + goal + reminds (maximum intervention women receive information about the goal of steps/day to be reached: 10,000-11,000. They will receive messages on the mobile phone remembering the goal to achieve and a notification that the researching staff will proceed to collect the average count of steps/day of the week prior to 20th and 32nd GW. Women will get recommendations on physical activity during pregnancy.

#### Arm 2

Intervention 2 (I2), minimum intervention: use of pedometer watch from 12th to 32nd GW (10 weeks). They will not receive goal information nor reminds to collect information from the pedometer. Women will be given recommendations on physical activity during pregnancy.

#### Arm 3

No Intervention, control group: without pedometer. Women will receive recommendations on physical activity during pregnancy.

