### Instruments

These are the main sources of information:

1) **Structured interview** that will be conducted in person at 13th, 20th and 32nd GW. The duration of the interviews will take approximately 35–40 min, which includes: the Athens Insomnia Scale (in English, AIS-8) [37], the Pittsburgh Sleep Quality Questionnaire [38], the Symptom Inventory in pregnancy [39, 40], short IPAQ [41], Adherence to the Mediterranean Diet, with Predimed questionnaire without wine [42]; 2) **Record of the average steps/day** of weeks 19 and 31 of gestation (information downloaded from the pedometer) and quantification of average hours of sleep at 19th and 31st GW (information downloaded from the Xiaomi Mi Band 2™ pedometer) (Fig. 1); 3) **Clinical history:** to collect the variables related to birth (tertiary outcome variables) and 4) Subsequent **telephone contact** if necessary (correction of missing data).

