### Outcome measures

Primary outcome measures in the three arms:

1) ***Prevalence of insomnia*** in third trimester of pregnancy (time frame: 32nd GW) will be evaluated with the Insomnia Athens Scale (IAS) [37], an eight-item scale that assesses the quantity and quality of sleep (first five items) and the diurnal repercussion of insomnia (daytime sleepiness, physical and mental functioning and well-being during the day). Each of the items scores from 0 to 3 (affectation of the item from light to severe). The total score ranges from 0 to 24 points, considering insomnia from a score equal to or greater than 6 points (Sensitivity = 93% and Specificity = 85%) or equal to or greater than 7 points (Sensitivity = 84% and Specificity = 90%).

2) ***Change in mean steps/day*** after intervention in the arms using pedometer register (time frame: 19th and 32nd GW).

Secondary outcome measures in the three arms (time frame: 12th, 19th and 32nd GW): ***Quality of sleep*** of pregnant women measure with the Pittsburgh Questionnaire (PSQI) [38], it assesses the quality of the individual’s sleep during the previous month. It consists of 19 items grouped into seven components: quality, latency, duration, efficiency and sleep disturbances, use of medication for sleep and diurnal dysfunction; each component is scored from 0 to 3, according to a Likert scale in which zero is the absence of the symptom and 3 is its maximum presence. This will result in a score that ranges from 0 to 21 points (the higher score, the worse sleep quality): a PSQI score of > 5 indicates poor sleep quality, with a diagnostic sensitivity of 89.6% and a specificity of 86.5%.

Other pre-specified outcome measures in the three arms:

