### Data analysis

A descriptive analysis of the variables collected in the study will be carried out. Measures of central tendency and dispersion will be calculated for the numerical variables and absolute and relative frequencies for the qualitative ones. The normality of the variables will be checked with the Kolmogorov-Smirnov test, in order to determine whether parametric or non-parametric tests will be carried out later. 95% confidence intervals (CI) will be obtained for both means and proportions.

For the contrast of the hypothesis of equality between the group of patients I1 and the group of patients I2, in terms of the number of daily steps and for each GW (19th and 31st), the Student t test will be used for independent samples or Mann-Whitney U, as appropriate. Subsequently, to assess whether there are differences between the groups with respect to the frequency of insomnia/quality of life for each trimester of pregnancy, the Pearson’s Chi-square test or Fisher’s exact test will be used when necessary.

On the other hand, to determine if differences are found between the quantitative variables (hours of sleep, quality of sleep) throughout the study period (first, second and third trimester) among the participants, the analysis of variance will be used for measurements repeated in the parametric case. In the case of having to use a non-parametric test, the Friedman test will be used. Subsequently, to assess the differences in the quality of life, for each of the groups, before starting the walking program and after finishing it (pre-post), the McNemar-Bowker test will be used.

For the contrast of the hypothesis of equality between the three groups of patients, regarding the weight gained during pregnancy (until 34 ^st^ GW), the weight of the newborn and the gestational week, an analysis of the variance or the test of Kruskall-Wallis will be used, as appropriate. In case of statistical significance, multiple comparisons will be obtained using the Student’s parametric test or the non-parametric Mann-Whitney U test applying Bonferroni correction.

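### The step-count primary outcome is defined as a change but tested as unadjusted levels at weeks 19 and 31, leaving the week-12 count unused and losing precision

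*Protocol article*

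**What the plan says.** In the Protocol article, Outcome measures lists as the second primary outcome a change in average daily steps "after intervention in the arms using pedometer register (time frame: 19th and 32nd GW"). It does not say what the change is measured from.

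Data analysis compares the two pedometer arms by a hypothesis test: "in terms of the number of daily steps and for each GW (19th and 31st), the Student t test will be used for independent samples". A rank test is the stated alternative. The Abstract repeats this plan: "Student t test or Mann-Whitney U will be used to compare 19th and 31st GW mean of daily steps between I1 and I2 groups". Neither place computes a change or includes a baseline.

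On what is recorded, the Abstract states "At 12th, 19th and 31st GW the average steps/day will be measured in groups I1 and I2". Instruments lists the average steps per day only "of weeks 19 and 31 of gestation (information downloaded from the pedometer"), so week 12 is missing there. The final reading is week 31 in the Abstract, Instruments and Data analysis, but week 32 in Outcome measures.

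Under Arms and interventions, I1 is described as "maximum intervention: pedometer + goal + reminds". Its messages include "a notification that the researching staff will proceed to collect the average count of steps/day of the week prior to 20th and 32nd GW". For I2 the article says "They will not receive goal information nor reminds to collect information from the pedometer".

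**The concern.** A primary outcome should be the quantity that is tested. Here one section names a change and the analysis tests two separate levels, and the sections disagree on whether a baseline reading exists and on the final week. A reader of the results could not tell whether a reported I1–I2 difference is the primary outcome or a substitute for it, and the reference week could be settled after the data are seen.

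Precision is also at stake. If week-12 steps are recorded before women learn their arm, they are an obvious covariate for later steps, and leaving them out makes the comparison noisier than it need be. The article itself expects 20–30% losses at the later interviews, so precision is worth protecting.

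A smaller question concerns what the difference means. The weeks that are scored are the ones I1 is told about and I2 is not.

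**Working it through.** **No step figure to reproduce.** The article gives no standard deviation, target difference or power for steps. Its 120 women per pedometer arm come from low compliance with activity recommendations, not from step counts.

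**Step 1. The passages side by side.**

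| Section | Quantity | Weeks |
|---|---|---|
| Outcome measures | change in mean steps | 19, 32 |
| Abstract, measurement | mean steps | 12, 19, 31 |
| Instruments | mean steps | 19, 31 |
| Abstract and Data analysis, test | level, I1 vs I2, unadjusted | 19, 31 |

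The quantity differs between definition and test, week 12 appears once, and the last week is 31 or 32.

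**Step 2. Relative variance.** Let r be the correlation between week-12 and later steps, with equal variances. Relative to the raw-level comparison (variance 1), a change score has variance 2(1 − r) and ANCOVA has 1 − r². The article gives no r, so a range is assumed.

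| r (assumed) | Change score 2(1 − r) | ANCOVA 1 − r² | Raw relative to ANCOVA, 1/(1 − r²) |
|---|---|---|---|
| 0.3 | 1.40 | 0.91 | 1.10 |
| 0.5 | 1.00 | 0.75 | 1.33 |
| 0.7 | 0.60 | 0.51 | 1.96 |

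ANCOVA is never worse than the raw comparison on this large-sample measure. A plain change score, which is the outcome as named, is worse than raw levels when r is below 0.5.

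**Step 3. The same in steps per day.** The smallest difference detectable with 80% power at two-sided 5% is (1.96 + 0.84) × SD × √(f × 2/n), where f is the variance factor from step 2. Take n = 120 per arm from Sample size, and n = 84 after 30% loss (120 × 0.7). SD = 3,000 steps/day is assumed.

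| n per arm | Raw | ANCOVA, r = 0.3 | r = 0.5 | r = 0.7 |
|---|---|---|---|---|
| 120 | 1,085 | 1,035 | 940 | 775 |
| 84 | 1,297 | 1,237 | 1,123 | 926 |

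For 120 per arm, assumed SDs of 2,500 and 3,500 give 904 and 1,266 for the raw test; the ratios to ANCOVA do not change. A change score at n = 120 and SD 3,000 gives 1,284, 1,085 and 840 at r = 0.3, 0.5 and 0.7.

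**Step 4. Does omitting the baseline bias the test?** No. In 5,000 simulated trials at each r (120 per arm, SD 3,000, no true difference), the mean errors of the raw, change-score and ANCOVA estimates were all within about 15 steps of zero. That is small against standard errors of about 275 to 460 and is consistent with no bias.

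**The case against.** The strongest reply is that the planned test is valid. Comparing raw levels between randomised arms is unbiased, so adjustment is a gain in efficiency and not the repair of an error. Covariates are also often left to an analysis plan. The validity point stands. The article, however, does fix the test, and that test does not match the outcome the article defines; a later plan would have to contradict one section or the other.

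The size of the gain is conditional. At r = 0.3 it is about 10%. Eligibility is restricted to women below the equivalent of 7,000 steps/day, which would tend to lower the correlation, so the upper end of the range is the less likely one.

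A reader might take the outcome literally as the change from week 19 to week 32, between two readings on intervention. That is possible but strained. A change after an intervention more naturally means a change from before it, and the Abstract supplies a week-12 reading. The defect is the unnamed reference week.

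A reader might also infer that the I1–I2 comparison is biased toward I1. The documents do not support that as a fact. Omitting the baseline causes no bias, so only the notice to I1 could. Reminders are declared I1 content, so the contrast can fairly be read as the effect of the whole package. The article does not say whether the notice arrives before or after the scored week; if after, it cannot alter that week's walking. What remains is a risk that the difference in announced weeks overstates sustained walking. Nor can that risk be scaled by the 2,000–2,500 steps quoted in the Background, because that figure compares pedometer users with non-users and both I1 and I2 wear one.

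**Conclusion.** The point holds as a mismatch between outcome and test, together with an avoidable loss of precision. The second primary outcome is a change without a reference week, the planned analysis tests unadjusted levels, and the week-12 count is named in one place and used nowhere in the step analysis. Relative to ANCOVA, the planned test's variance is 1.10 to 1.96 times as large over assumed correlations of 0.3 to 0.7. This rests on week 12 being a usable pre-allocation baseline, which the article leaves unclear: allocation is placed at week 12, I2's pedometer wear also starts at week 12, and the Abstract starts the intervention at week 13.

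The comparison is not invalid. The I1-only notice is a secondary caveat about interpretation: it carries a risk of unknown size and is not a demonstrated bias. The plan should be corrected before the step data are analysed.

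**What to change.** 1. In Outcome measures, state one step outcome with one set of weeks, reconciling 31 with 32: for example, mean steps/day at week 31, with week 19 also reported, compared between I1 and I2 and adjusted for baseline.
2. Add the week-12 record to Instruments and say whether it is taken before allocation and before I1 learns its goal.
3. In Data analysis, replace the unadjusted tests with ANCOVA, or a mixed model over weeks 19 and 31, with week-12 steps as covariate.
4. Make step 3 conditional on the timing. If the week-12 reading comes after allocation or goal-setting, adjusting for it could remove part of the effect. Use another activity measure taken before allocation instead, such as the first-interview IPAQ. Its timing must be confirmed too, because the first interview is placed at week 12 in one section and week 13 in others.
5. State that the I1–I2 difference is the effect of the whole I1 package in weeks announced to I1. Where the device record allows, add a sensitivity analysis on steps from other weeks between 12 and 32.

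Items 1 to 4 cost only wording and a covariate the Abstract says is already collected. Item 5 needs a longer device download, if those data are stored, which the article does not say. None of this changes what either arm receives, which matters because recruitment began in June 2019.

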### Data analysis

A descriptive analysis of the variables collected in the study will be carried out. Measures of central tendency and dispersion will be calculated for the numerical variables and absolute and relative frequencies for the qualitative ones. The normality of the variables will be checked with the Kolmogorov-Smirnov test, in order to determine whether parametric or non-parametric tests will be carried out later. 95% confidence intervals (CI) will be obtained for both means and proportions.

For the contrast of the hypothesis of equality between the group of patients I1 and the group of patients I2, in terms of the number of daily steps and for each GW (19th and 31st), the Student t test will be used for independent samples or Mann-Whitney U, as appropriate. Subsequently, to assess whether there are differences between the groups with respect to the frequency of insomnia/quality of life for each trimester of pregnancy, the Pearson’s Chi-square test or Fisher’s exact test will be used when necessary.

On the other hand, to determine if differences are found between the quantitative variables (hours of sleep, quality of sleep) throughout the study period (first, second and third trimester) among the participants, the analysis of variance will be used for measurements repeated in the parametric case. In the case of having to use a non-parametric test, the Friedman test will be used. Subsequently, to assess the differences in the quality of life, for each of the groups, before starting the walking program and after finishing it (pre-post), the McNemar-Bowker test will be used.

For the contrast of the hypothesis of equality between the three groups of patients, regarding the weight gained during pregnancy (until 34 ^st^ GW), the weight of the newborn and the gestational week, an analysis of the variance or the test of Kruskall-Wallis will be used, as appropriate. In case of statistical significance, multiple comparisons will be obtained using the Student’s parametric test or the non-parametric Mann-Whitney U test applying Bonferroni correction.

Finally, a bivariate mixed-effects logistic regression model will be carried out to determine which variables influence the greater frequency of insomnia, considering the latter quantitatively. To delimit the extent to which the associations that appear are explainable by the effect of the rest of the variables included in the study, a multivariate mixed-effects logistic regression model will be constructed. 95% confidence intervals (CI) will be obtained. All contrasts will be bilateral and statistical significance will be considered when the *p* value is ≤0.05. The data analysis will be carried out by intention to process and by protocol, using the Stata / SE v15.0 statistical package.

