1. ***Quality of life*** of women through pregnancy (time frame: 12th, 19th and 32nd GW), measure with the Pregnancy Symptom Inventory (PSI) [39, 40]: 41-item Likert scale developed from a group of experts and focus groups. It registers the range of symptoms that appears in the last month (Likert scale from 0 to 4: never, rarely, sometimes, often) and its impact on quality of life, by affecting the activities of daily life (scale Likert from 0 to 3: it does not limit me, it limits me a little, it limits me a lot). It has been adapted to Spanish pregnant women and is reliable (Kappa coefficient range = 0.6–0.9) [40]; 2. ***Women weight gain*** in kilograms (time frame: 12th and 32nd GW), measured with the hospital scale; 3. ***Weight of the new-born*** (time frame: delivery) collected from the clinical history of the women; 4. ***Gestational week at delivery*** (time frame: delivery) collected from the clinical history of the women.

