## Discussion

Currently, about 60% of pregnant women have insomnia towards the end of pregnancy [1–4]. This study aims to reduce the prevalence of insomnia in the third trimester of pregnancy by 33% in the pedometer + goal group (maximum intervention) and, on the other hand, to reduce the prevalence of insomnia by 16.6% in the pedometer-only group (minimum intervention), compared to the control group (usual advice without pedometer).

Women in the maximum intervention group are expected to have 33% less insomnia in the third trimester of gestation compared to pregnant women in the control group. Furthermore, in the intervention groups, sleep quality will improve (Pittsburgh score < 5) [38], the frequency of symptoms associated with pregnancy (asthenia, anxiety, cramps) will decrease and the performance of daily life activities (measured with the PSI questionnaire) will improve, compared to the control group.

The intervention requires health professional to explain the use of the pedometer and establish a therapeutic alliance with the pregnant woman to reach a goal. The benefits are expected to be obtained during the project and after its completion: 1) During the project, since the participating women will increase their motivation to walk, due to the use of the pedometer, and will benefit from the inclusion of PA in their daily life, such as decreased sedentary lifestyle and weight control in pregnancy. This will even encourage the practice of walking from their closest social or family bond: 2) In the short term, we will know if the expected potential change has managed to reduce the prevalence of insomnia in the third trimester of pregnancy, by at least 33%.

Direct and indirect costs are expected to be saved: 1) Direct cost in pregnant women enrolled in the study —decreasing sleep-related disorders, increasing quality of sleep, quality of life and general well-being; 2) Indirect costs for the Andalusian Health Service: reduction in the number of visits in Primary Health Care derived from the direct consequences of walking during pregnancy, cost reduction in drugs related to the discomfort of pregnancy. Depression, pregnancy weight control, pregnancy-induced high blood pressure, or back pain will be mitigated by promoting pregnancy walking.

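### Quality of life (PSI) responses are ordered, but the only between-arm test named for them ignores order; if more than two levels are analysed, this costs power and leaves no ordinal effect estimate

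*Protocol article*

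**What the plan says.** Outcome measures lists quality of life among the other pre-specified outcomes, measured with the 41-item PSI. Symptom frequency is recorded on a "Likert scale from 0 to 4: never, rarely, sometimes, often", and impact on daily activities on a "scale Likert from 0 to 3: it does not limit me, it limits me a little, it limits me a lot". Both sets of labels are ordered. No cut-off is given for the PSI, whereas the same section gives cut-offs for the insomnia scale and the sleep-quality index.

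Data analysis handles insomnia and quality of life in one sentence, whose stated purpose is "to assess whether there are differences between the groups with respect to the frequency of insomnia/quality of life for each trimester of pregnancy". For both outcomes it names Pearson's chi-square, with Fisher's exact test as the fallback. The Methods part of the Abstract repeats this. The other PSI analysis is within each arm: "before starting the walking program and after finishing it (pre-post), the McNemar-Bowker test will be used". Rank tests are named for steps, weight gain, newborn weight and gestational week, and Friedman for sleep measures. None is named for the PSI, and the regression models are for insomnia.

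The expectation is directional. The hypothesis in Background is that the programme improves quality of life, and the Discussion expects that "the performance of daily life activities (measured with the PSI questionnaire) will improve, compared to the control group".

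**The concern.** Insomnia defined by a cut-off is binary, so chi-square or Fisher suits it. The PSI answers are of another type, yet the combined phrase gives them the same test. Pearson's statistic is unchanged if the category labels are shuffled, so it spreads its sensitivity over every possible departure from equality, including patterns that are neither better nor worse. With three arms and k levels it has (3 − 1)(k − 1) degrees of freedom: 4 for three levels and 6 for four. Kruskal-Wallis or a proportional-odds test of arm has 2.

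If the programme moves women along the scale as expected, the planned test is less likely to detect it. Nor does it come with a single measure of how far the distribution has moved. The control arm is small and losses of 20–30% are expected, so there is little power to spare.

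**Working it through.** **No figure to reproduce.** The article gives no PSI effect size, distribution or power. Its sample size (120, 120 and 25) rests on low compliance with activity recommendations. The size of the loss must therefore be shown under stated assumptions.

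**Inputs from the article**
- Total of 265, allocated 1:4:4 in blocks of nine (Sample size; Randomization of participants and concealment): 265 × 4/9 ≈ 118 in each of I1 and I2, and 265 × 1/9 ≈ 29 in C.
- Two-sided test at 5%.
- Levels: three labels for limitation and four for frequency. The printed code ranges (0 to 3 and 0 to 4) would allow one more each, so the level count is itself uncertain.

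**Assumptions**
- Proportional odds: logit P(Y ≤ j) = α_j + β, with level 1 the best, β = 0 in C, ln(OR) in I1 and ½ ln(OR) in I2.
- Control distributions as listed in the table.

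**Worked case: four even levels, I1 OR 2.25.** Control cumulative odds of 1/3, 1 and 3 are multiplied by 2.25 in I1 and by √2.25 = 1.5 in I2.
- I1: 0.429, 0.264, 0.179, 0.129
- I2: 0.333, 0.267, 0.218, 0.182
- C: 0.25 each
- Weighted mean: 0.367, 0.264, 0.204, 0.166

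Pearson non-centrality: λ = Σ n_i Σ (p_ij − p̄_j)²/p̄_j = 5.87. On 6 df (critical value 12.59) this gives 39% power. Nearly the same signal on 2 df (critical value 5.99) would give 57%. The loss is the cost of the four extra degrees of freedom.

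**Simulation.** 20,000 trials per cell, arms 118/118/29, Pearson versus tie-corrected Kruskal-Wallis on the same tables:

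| Control distribution | I1 OR | Pearson % | Kruskal-Wallis % | Loss (points) |
|---|---|---|---|---|
| 3 even | 1.5 | 13.0 | 16.7 | 3.7 |
| 3 even | 2.25 | 44.4 | 54.6 | 10.1 |
| 3 even | 3.0 | 71.9 | 81.0 | 9.2 |
| 50/35/15 | 1.5 | 14.0 | 16.3 | 2.4 |
| 50/35/15 | 2.25 | 40.9 | 49.4 | 8.5 |
| 50/35/15 | 3.0 | 64.5 | 73.3 | 8.8 |
| 80/15/5 (symptom mostly absent) | 1.5 | 11.0 | 11.9 | 0.9 |
| 80/15/5 | 2.25 | 24.6 | 28.3 | 3.7 |
| 80/15/5 | 3.0 | 36.7 | 43.0 | 6.3 |
| 4 even | 1.5 | 12.3 | 17.9 | 5.7 |
| 4 even | 2.25 | 40.9 | 56.9 | 16.0 |
| 4 even | 3.0 | 68.4 | 83.5 | 15.1 |
| 10/20/40/30 | 1.5 | 10.7 | 17.4 | 6.7 |
| 10/20/40/30 | 2.25 | 37.9 | 57.1 | 19.2 |
| 10/20/40/30 | 3.0 | 67.1 | 84.0 | 16.8 |

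(Losses were taken before rounding.)

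- **With attrition** (90/90/22, 202 of 265, about 24% loss), OR 2.25 to 3.0: 6.8 to 10.3 points for the spread three-level cases and 14.4 to 19.2 for four levels. For 80/15/5 it is 2.8 to 4.3, and 0.5 at OR 1.5.
- **Two levels:** the difference is within 0.4 points of zero, so dichotomised items lose nothing.
- **No effect (OR 1):** both tests reject in about 5% of trials.
- **Pairwise, with the effect set so that the rank test has 50% or 80% power:** I1 vs I2 loses about 9–11 points (three levels) or about 16 (four); I1 vs C loses about 4–8 or 10–13.

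**The case against.** The strongest objection is that the analysed variable is not stated. The article says how items are recorded, not whether single items, a domain, a total or the proportion limited by a symptom enters the between-arm test. Placing quality of life beside insomnia, which is a cut-off variable, is compatible with comparing proportions, and a condensed article may leave that reduction to the full protocol. A reader might take McNemar-Bowker as proof that multi-level categories are compared between arms. It is not proof: Bowker's test reduces to McNemar's at two levels and is named only for the within-arm comparison. It suggests that more than two levels are kept, and no PSI cut-off is given, but the point stays conditional.

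Second, a reader might infer that the trial simply loses 6 to 20 points of power. The article does not support an unconditional figure. That range needs large effects, spread categories and a proportional-odds shift, a model that favours rank tests; with small effects or rare symptoms the loss is much smaller.

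Third, Kruskal-Wallis is also a non-directional omnibus test and also ignores the ordering C, I2, I1 of the arms. The plan already promises relative frequencies and 95% confidence intervals for proportions, from which direction can be read. This stands. The better-or-worse argument therefore favours an ordinal effect estimate, not a rank test on its own.

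Fourth, chi-square and Fisher are legitimate tests of equal distributions, the outcome ranks below the primary and secondary ones, and the sample size was not set on it. All true, and the reason the point is minor. It does not fall away as omitted detail, because a specific test is stated in both the Abstract and Data analysis.

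**Conclusion.** The point holds in conditional form. Where PSI responses are compared between arms with more than two levels, chi-square or Fisher is a valid but inefficient choice for the shift the trial expects. With arms of about 118/118/29 and an assumed proportional-odds shift, the loss against Kruskal-Wallis is about 6 to 20 points for I1 odds ratios of 2.25 to 3.0 with spread categories, about 0.5 to 7 points for an odds ratio of 1.5 or rare symptoms, and nil for dichotomised items. A reader might infer that the planned comparison is invalid or raises the false-positive rate; the no-effect simulation shows that it does not. Severity: a worthwhile improvement, not a flaw that threatens the trial's conclusions.

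**What to change.** In Data analysis and in the Methods part of the Abstract, separate insomnia from quality of life.

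- Keep Pearson's chi-square or Fisher's exact test for binary insomnia.
- State the form in which the PSI is analysed.
- For multi-level PSI frequency and limitation responses, compare arms with a proportional-odds model, reporting a common odds ratio with 95% confidence interval for each arm comparison. Kruskal-Wallis with pairwise Mann-Whitney tests is an acceptable alternative, though it supplies no odds ratio.

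The cost is a sentence or two of wording and no new data; rank tests are already used elsewhere in the plan. The downside is less sensitivity to non-monotone differences between arms, which the trial does not hypothesise.

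### The only secondary outcome, PSQI sleep quality, is given a test of change over pregnancy and no comparison between the randomised arms

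*Protocol article*

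**What the plan says.** Outcome measures introduces PSQI under "Secondary outcome measures in the three arms (time frame: 12th, 19th and 32nd GW", and no other secondary outcome is listed. Data analysis groups quality of sleep with hours of sleep and plans to look for differences "throughout the study period (first, second and third trimester) among the participants, the analysis of variance will be used for measurements repeated". It then adds: "In the case of having to use a non-parametric test, the Friedman test will be used". The abstract has the same plan: "To determine differences in hours of sleep and quality of sleep throughout each trimester of pregnancy, analysis of variance or Friedman test will be used".

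Quality of life (PSI) gets two analyses. One compares the arms with chi-square or Fisher, "to assess whether there are differences between the groups with respect to the frequency of insomnia/quality of life for each trimester of pregnancy". The other works inside each arm: "for each of the groups, before starting the walking program and after finishing it (pre-post), the McNemar-Bowker test will be used".

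The Discussion states its expectations as contrasts with control. Sleep quality is to improve in the intervention groups, and daily activities "measured with the PSI questionnaire) will improve, compared to the control group".

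**The concern.** A randomised trial supports a claim about its programme through a comparison of arms. For PSQI, the stated test asks whether scores differ between trimesters among the women as a whole. A significant result could reflect the ordinary course of pregnancy, and a non-significant one could hide arms moving in different directions. Some worsening is plausible in every arm: the Background puts insomnia at about 40% early in pregnancy and above 60% in the third trimester, and women with insomnia at the start are excluded. If the plan is followed as written, the secondary outcome yields no estimate of an intervention effect.

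The pre-post quality-of-life test carries a smaller risk. It gives one p value per arm, and the arms differ greatly in size, so setting those p values side by side could be mistaken for a comparison of arms.

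**Working it through.** **1. Which tests in the article compare arms?**

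| Outcome | Test named | Arms compared? |
|---|---|---|
| Steps/day, weeks 19 and 31 | t test or Mann-Whitney | Yes, I1 with I2 |
| Insomnia, each trimester | Chi-square or Fisher | Yes |
| Quality of life, each trimester | Chi-square or Fisher | Yes |
| Quality of life, pre-post | McNemar-Bowker | No, within each arm |
| Hours of sleep, sleep quality (PSQI) | Repeated-measures ANOVA or Friedman | None named |
| Weight gain, newborn weight, gestational week | ANOVA or Kruskal-Wallis | Yes, three groups |
| Insomnia, mixed-effects models | Logistic | Insomnia only, not PSQI |

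The text names the groups wherever it compares them. For PSQI it names trimesters. Friedman ranks the repeated values within each woman and has no place for a between-woman factor such as arm.

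**2. What does a pooled time test respond to?** Simulation with the arm sizes in Sample size (120, 120, 25), two-sided 0.05, 2,000 runs. Assumptions not in the documents: normal score, SD 3, correlation 0.5 between visits.

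| True change, first to third visit | Pooled Friedman rejects | Between-arm ANOVA of change rejects |
|---|---|---|
| None in any arm | 5% | 4.5% |
| +1.0 in every arm | 99% | 5% |
| +1.5 in every arm | 100% | 5.5% |
| I1 −1, I2 +1, C 0 | 5% | 99.8% |

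The second and third rows contain no arm effect. The last row is built so that the pooled change cancels: (120 × (−1) + 120 × 1 + 25 × 0) / 265 = 0. It shows what the test can miss; it is not a forecast.

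**3. Within-arm p values with unequal arms.** The randomisation section lists one C, four I1 and four I2 per block of nine. Of 265 women that is 265 × 4/9 ≈ 118 in I1 and 265 × 1/9 ≈ 29 in control, a ratio of 29/118 ≈ 0.25. (Sample size gives 120 and 25.) Suppose every arm has the same true change of d SDs of within-woman change, tested by a paired t test in each arm. The arms are independent, so

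P(I1 significant, C not) = power(118, d) × (1 − power(29, d)).

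| d | Power, n = 118 | Power, n = 29 | I1 significant, C not |
|---|---|---|---|
| 0.1 | 0.190 | 0.082 | 17% |
| 0.2 | 0.577 | 0.180 | 47% |
| 0.3 | 0.898 | 0.345 | 59% |
| 0.4 | 0.991 | 0.548 | 45% |
| 0.5 | 1.000 | 0.739 | 26% |
| 0.6 | 1.000 | 0.877 | 12% |

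For example, at d = 0.3: 0.898 × (1 − 0.345) = 0.588. A McNemar simulation nearer to the planned test (120, 120, 25; 30% worsening and 12% improving in every arm, both assumed; 4,000 runs) was significant in 88%, 88% and 26% of runs. Identical change thus gives very different p values through arm size alone.

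**4. Hours of sleep.** Instruments describes pedometer sleep at weeks 19 and 31, and the control arm has no pedometer. PSQI has a duration component and is collected in all arms at three visits. Data analysis does not say which source is meant.

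**The case against.** The strongest reply is that repeated-measures ANOVA can carry an arm factor and an arm-by-time term, and that a condensed article may not spell them out while a fuller analysis plan, not shown, does. This stands in part. But the article does state a test, describes it as a comparison of trimesters, and pairs it with a fallback that cannot compare arms, so the stated plan needs correcting whatever else exists. Both primary outcomes do have tests between groups, which confines the gap to the secondary outcome.

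Four stronger readings are tempting and are not supported:

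- *Quality of life has no between-arm test either.* It has one, the chi-square or Fisher comparison at each trimester. McNemar-Bowker is an addition to it and not the only test behind the Discussion's claim.
- *The time effect will be significant whatever the programme does.* The 40% and 60% are insomnia prevalences, not PSQI scores. Eight of every nine women receive a pedometer, so a programme that prevented worsening would shrink the pooled time effect.
- *The three-trimester test of hours of sleep cannot be run.* That holds for the pedometer measure only; PSQI duration is available in all arms at three visits.
- *The plan has a 59% chance of a false pattern.* That figure is near the peak of a curve from 12% to 59%. It uses a paired t test the plan does not specify, and the article nowhere says that within-arm p values will be compared between arms.

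**Conclusion.** The point holds for PSQI. Its stated analysis addresses change over pregnancy, names no arm contrast, and in the Friedman case cannot have one, so it cannot show or isolate the effect relative to control that the Discussion expects. This follows from the wording and the structure of the tests and does not depend on the simulation, whose SD, correlation and trends are assumed.

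For quality of life the point is only one of emphasis: the between-group comparison should carry the intervention conclusion. With control about a quarter the size of I1, differing within-arm p values do not show an arm difference. The 12% to 59% range (common change of 0.1 to 0.6 SD, 118 and 29 women, no losses) is illustrative. For hours of sleep, the source has to be stated before the right comparison can be fixed.

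**What to change.** - **PSQI.** Replace the stated test with a between-arm analysis, for example a linear mixed model on the 20 and 32 GW scores with arm, visit, arm × visit and baseline PSQI. Report adjusted differences I1–C, I2–C and I1–I2 at 32 GW with 95% CI. Do not use Friedman for this purpose.
- **Quality of life.** State that the intervention conclusion rests on the between-group comparison already planned, and keep the McNemar-Bowker results as description.
- **Hours of sleep.** State the source. If it is the pedometer, compare I1 with I2 only, at weeks 19 and 31. If it is PSQI duration, analyse it between arms in the same way as PSQI.

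The cost is revised wording and some programming in the software already named, with no new data. The small control arm will show in the intervals: without baseline adjustment or losses, the 95% half-width for I1–C is about 1.96 × √(1/118 + 1/29) ≈ 0.41 SD.
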